**Figure 2. F2:**
[figure not shown]
Timeline of enrollment, assessments, intervention, and follow-up. ABI: ankle-brachial index; CVD: cardiovascular disease; eGFR: estimated glomerular filtration rate; HbA_1c_: hemoglobin A_1c_.

#### A Nurse-Led Tailored Self-Management Session

This management session will involve (1) a health assessment to identify the needs of participants, (2) an interactive face-to-face education and self-management consultation responsive to individual health needs, (3) a mindfulness-based SKT meditation healing exercise training, and (4) a digital device training. A family doctor will conduct a physical examination, and a nurse will conduct a structured interview. A self-management session focuses on lifestyle management based on the DASH diet, tailored to address the individual needs of individuals with diabetes and chronic renal disease. It includes physical exercise, sleep improvement, and training in self-management skills.

#### A Real-Time Knowing Your Numbers Strategy

This study component comprises the use of a smartwatch, a smartphone health app, and a salt meter. We will ask participants to use these digital devices for 6 weeks.

##### A Smartwatch: Huawei Watch Fit 3

This study will use the commercialized Huawei Watch Fit 3 and its associated HUAWEI Health app (Huawei Technologies Co, Ltd). Study participants will use this smartwatch and its smartphone app to collect daily reference data on physical activity, sleep quality, heart rate, and stress levels, which will guide their daily self-management efforts and actions in line with their target setting with the nurses. The device features a built-in interactive function that allows each participant to set goals for exercise, physical activity, and sleep. The health app helps participants track their progress and compare milestones on a weekly and monthly basis. For instance, if a participant misses a walking target, they can take additional steps in their daily routine. Participants can continue using the health app to track their physical activity after using this wearable device. Similarly, participants can use sleep information from a prior night to improve their sleep hygiene.

##### Portable Salt Measurement Device: CHEM Meter or Salt Meter

CHEM Meter (Quality Assembly Co, Ltd; Figure 3) is a portable salt measurement device using a parts per million/total dissolved solids meter with total dissolved solids expressed in parts per million by measuring the electrical conductivity of sodium chloride (%NaCl) in grams per 100 milliliters (g/100 ml) in food and converting into parts per million unit [34]. The devices use the alternating electrical current, which has a high frequency, to accurately determine the concentration of sodium chloride and display the result in emotional facial graphics; smile, poker face, and frown for sodium chloride content between <0.7%, 0.7%‐0.9%, and >0.9%, respectively [31] (Figure 4). This design is easy to understand for all users. The researchers require all participants to use a salt meter to test sodium levels in their food before meals and adjust their food consumption accordingly to limit daily sodium intake based on their individual health needs.

**Figure 3. F3:**
[figure not shown]
Chem meter m device used in this study (Quality Assembly Co, Ltd).

**Figure 4. F4:**
[figure not shown]
Examples of the CHEM meter facial display intended to show sodium chloride (NaCl) concentration in the interested food; smile for the NaCl <0.7%, poker face for NaCl of 0.7%‐0.9%, and frown for NaCl >0.9%.[35]

### The SKT Meditation Healing Exercise

The SKT is a meditation-based intervention aimed at improving vascular health, particularly in individuals with hypertension [36]. This technique involves a standing deep breathing meditation exercise, which has significantly reduced both systolic and diastolic BP in patients with uncontrolled hypertension and diabetes. The SKT technique is effective when practiced for 20 minutes, twice daily, for 8 weeks. This approach provides a nonpharmacological option for managing BP, a critical factor in maintaining vascular health. A study involving 43 patients with uncontrollable hypertension showed that those who practiced the SKT technique experienced a significant reduction in both systolic and diastolic BP after 8 weeks, compared to a control group that only received medication [37].

### A Vascular Care Self-Management Manual

The self-management manual is a color-printed A5-sized manual. The researchers developed this manual based on the study’s self-management components to assist the study participants in maintaining the desired management. The manual includes easy-to-use information on the DASH diet, a compatible list of local foods, a step-by-step pictorial SKT meditation healing exercise, information on physical activity and exercise, and an approach to improve sleep quality. The researchers developed this manual based on a literature review. A panel of 5 experts, comprising 2 family medicine doctors, 1 NCD nurse case manager, and 2 nutritionists, reviewed the manual. The researcher revised the manual based on expert suggestions and comments before production. Participants will use digital-based information as a reference to adjust their self-management behaviors in response to the tailored interventions offered by the nurses.

Participants will receive a smartwatch, a salt meter, and printed manuals to support guidance on dietary and physical activity, stress management, and sleep management. All enrolled participants will attend a face-to-face session. The digital components last for 6 weeks. After 6 weeks, we will ask all participants to continue their dietary, physical activity, stress management, and sleep management behaviors based on the information they gained from the digital components during the previous 6 weeks. All participants will record their daily diet and exercise using the printed diary.

### Recruitment

Researchers are recruiting participants for this study from primary care clinics in Nakhon Ratchasima, Thailand. The nurses at the primary care clinics will screen potential participants to determine if they meet the inclusion criteria. If the potential participants are deemed eligible and willing to participate in the study, the nurses will refer them to the researcher. Next, the researcher will approach potential participants who meet the inclusion and exclusion criteria to inform them about the study details, obtain written informed consent, and assess their digital health literacy. Those who pass all inclusion and exclusion criteria are eligible for recruitment into the study.

### Inclusion and Exclusion Criteria

The inclusion and exclusion criteria are present in Textbox 1.

Textbox 1.Inclusion and exclusion criteria.
**Inclusion criteria**
Aged ≥20 years with noncommunicable disease, both man and woman.Determined as having a mild to moderate risk for vascular complications, including having at least 1 condition such as uncontrolled diabetes, high blood pressure, hyperlipidemia, a family history of vascular or heart disease, or smoking, or being aged over 50 years. A nurse will assess these risks using the Thai cardiovascular risk score, while a family doctor will confirm eligibility by reviewing the medical history of patients.Have access to a smartphone.Able to use digital devices and communicate in Thai.Having the intention to change self-management behaviors according to verbal screening.Able to provide informed consent.
**Exclusion criteria**
Acute medical condition requiring hospitalization.Cognitive impairment or inability to participate.Already enrolled in a similar program.Recently diagnosed with strokes, hypertensive heart disease, ischemic heart disease, heart failure, acute myocardial infarction, and psychotic disorder.Having inadequate digital health literacy as measured by the eHealth Literacy Scale. The cut-off points of <26 indicate inadequate digital health literacy [38].

### Setting and Participant Demographics

Participants include individuals at risk of CVDs, such as uncontrolled hypertension, hyperlipidemia, and diabetes, who live in the urban and suburban communities of Nakhon Ratchasima province of Thailand. Residents of these communities have diverse educational backgrounds and socioeconomic statuses. In this setting, the younger generation typically holds an associate’s degree; the middle group is educated primarily at a lower level, often with labor-intensive work, whereas the older generation has slightly better education, with an average ranging from an associate’s degree to a bachelor’s degree.

### Sample Size Calculation

The primary outcome of this study is the change in the self-management behavior score from baseline to 12 weeks postintervention. The sample size was calculated for a paired-samples within-group design using G*Power. Based on previous studies evaluating digital and nurse-led interventions to improve self-management in individuals with chronic conditions [27], a moderate effect size (Cohen *d*=0.5) was assumed. With a significant level of 0.05, 80% power (1-β=.80), and a Cohen *d*=0.5 effect size, the required sample size to detect a change is 34. Allowing for a 30% attrition rate, the sample size was adjusted to 45 participants.

### Data Collection Procedures

Researchers will collect information on CVD risk, sleep quality, stress levels, and food consumption, as well as self-management behaviors, using physical examinations, questionnaires, and semi-structured interviews at baseline and the conclusion of the study.

The research team will collect CVD risk information using health reviews and questionnaires.Digital data will be collected using the Huawei Watch Fit 3, which is associated with the HUAWEI Health app. These data do not include participant identification information. The researchers will access digital health data, including physical activity, sleep patterns, heart rate, and stress levels, through the HUAWEI cloud system. Data encryption will be used to protect data from unauthorized access, theft, or modification by scrambling it into an unreadable format that can only be decrypted with a special key.Sodium consumption: participants will use a CHEM meter to measure the salt concentration in their food before meals and record their sodium intake in their food diary.Participants will record their mindfulness activity, diet, and exercise data in a self-management diary.

Participants will be monitored weekly for 6 weeks through a health volunteer visit and a web-based survey. For the primary outcome, participants will answer questions about their self-management behaviors during (1) an initial medical screening; (2) at the end of weeks 1, 2, 3, 4, 5, and 6; (3) immediately after digital treatment at the end of week 6; and (4) week 12. For clinical outcomes, the primary end point is assessed at the end of week 12 (short-term outcomes), and the secondary end point is evaluated at week 24 (delayed outcomes) after the intervention is initiated. Clinical outcomes will include BP, BMI, lipid profiles, lipid ratio, HbA_1c_, ankle-brachial index, estimated glomerular filtration rate, and CVD risk. Acceptability will be assessed using a semistructured in-depth interview by researchers.

### Method of Measurement

The research instruments consist of (1) screening measurements, (2) experimental measurements, and (3) data measurements.

#### Screening Measurements

##### The eHealth Literacy Scale

Electronic health literacy is “*the ability to seek, find, understand, and appraise health information from electronic sources and apply the knowledge gained to addressing or solving a health problem*” [39]. Norman and Skinner [39] developed the eHealth Literacy Scale (eHEALS) measurement, which researchers will use to screen the digital health literacy of qualified participants. The eHEALS consists of 8 items rated on a Likert scale ranging from 1 (strongly disagree) to 5 (strongly agree). Possible scores range from 8 to 40, with a cut-off point of 26 or higher indicating adequate digital health literacy [38]. The Department of Health, Ministry of Public Health, subsequently translated the eHEALS into Thai. The Thai eHEALS has a test-retest reliability of 0.85 [40].

To ensure participants can safely and effectively engage with the digital intervention, participants will be required to score 26 or higher on the eHEALS to affirm high intent to use digital tools during the screening process. This threshold is applied pragmatically to maximize engagement and minimize attrition during the intervention phase, which is crucial for assessing the intervention’s initial efficacy signal.

##### The Thai Cardiovascular Risk Score

The Thai Cardiovascular Risk score was developed based on cohorts collected from the Electricity Generating Authority of Thailand study and validated using the 2nd and 3rd Electricity Generating Authority of Thailand cohorts, respectively [41]. The Thai health system has been practically using the Thai Cardiovascular Risk score as a reliable tool to forecast the risk of having a cardiovascular event in the future for Thais nationwide. The developer classified the risk as low risk (0%-10%), moderate risk (10%-20%), high risk (20%-30%), very high risk (30%-40%), and extremely high risk (40% or more).

### Experimental Measurement

The study will implement a self-management intervention comprising digital health components and a nurse-led face-to-face component among Thai participants. This study will use the Huawei Watch Fit 3 to collect digital data, including physical activity, sleep, heart rate, and stress level, and a CHEM (salt) meter to measure salt concentration in food.

### Data Measurements

#### The Demographic Data Form

Researchers developed this form to collect demographic data. The form includes a structured set of questions asking about gender, age, education, occupation, income, income adequacy, medical history, medication use, and underlying diseases.

#### The Dietary Behavior Screening (Sweet, Fatty, Salty) Questionnaire

The researchers will use the Dietary Behavior Screening (Sweet, Fatty, Salty) Questionnaire (DBSQ) to examine the dietary behavior of Thais with NCD. The Raipoong Academy, in collaboration with the Royal College of Physicians of Thailand, developed the DBSQ for public use as part of the Prevention & Health Promotion campaign. This measurement consists of 15 items: 5 items for sweet, 5 for fatty, and 5 for salty diet [42]. This measurement uses a 3-category Likert scale, from 1‐3 (1=“not at all” and 3=“always” for negative behaviors; and 3=“not at all” and 1=“always” for positive behaviors). The response choices for all items are standardized on a scale from 5 to 15, with scores of 6 to 9, 10 to 13, and 14 to 15 indicating mild-to-moderate, high, and critical dietary behavior risk, respectively. This study will examine the reliability of the DBSQ using 30 Thais with NCDs and obtain the Cronbach α coefficient before collecting the data.

#### Sleep Quality: The Thai Pittsburgh Sleep Quality Index

The Pittsburgh Sleep Quality Index (PSQI) is a 19-item self-report questionnaire that evaluates various aspects of sleep over the past month. The questionnaire assesses perceived sleep quality, sleep habits, such as habitual bedtimes and wake times, and sleep disturbances, including difficulty falling asleep, disordered breathing, nightmares, and pain [43]. A habitual bed partner is also required to rate 5 challenging questions about sleep, such as loud snoring, pauses in breathing, leg twitching, and disorientation during sleep. A scoring procedure generates scores for 7 distinct components: subjective sleep quality, sleep latency, sleep duration, habitual sleep efficiency, sleep disturbances, use of sleeping medication, and daytime dysfunction.

Component scores range from 0 (no difficulty) to 3 (severe difficulty), and their sum produces a global score ranging from 0 to 21, with higher values indicating poorer sleep quality. A PSQI score greater than 5 is considered indicative of poor sleep quality, based on its high sensitivity and specificity in identifying patients with sleep complaints [43]. Researchers developed the Thai-PSQI using a standardized method to measure major sleep disorders in Thai patients. The Thai-PSQI has a Cronbach α of 0.837 and test-retest reliability (intraclass correlation coefficient=0.89) [44]

#### The CVD Self-Management Behavior Questionnaire

The primary investigator developed the CVD Self-Management Behavior Questionnaire to examine self-management behaviors among Thais at risk of CVD. This measurement comprises 17 items: 4 related to exercise behaviors, 6 to dietary habits, 5 to treatment compliance (rational medication use), and 2 to smoking behaviors. This measurement uses a 6-category Likert scale, ranging from 0 to 5 (0=“not at all” and 5=“always”). The response options for all items are standardized, with higher scores indicating better CVD risk-prevention behavior. The researcher will test the CVD Self-Management Behavior Questionnaire for reliability with 30 Thais at risk of CVD and obtain a Cronbach α coefficient before collecting the data.

#### The Thai Stress Questionnaire (ST-5) or Srithanya Stress Test–5 Items

Srithanya Psychiatric Hospital developed this self-administered brief questionnaire to assess perceived stress levels [45]. The Stress Questionnaire-5 (ST-5) comprises items related to sleep problems, decreased concentration, irritability, boredom, and feelings of isolation. It measures subjective feelings over the past 2 to 4 weeks, using a 4-point Likert scale (0‐3) for each item. The total score is then categorized to indicate the level of stress experienced by the individual: 0 to 4 indicates mild stress, 5 to 7 indicates moderate stress, 8 to 9 indicates severe stress, and 10 to 15 indicates extremely severe stress. The ST-5 has a Cronbach of 0.85 [45].

#### An Automatic BP Measurement

A health volunteer will use the Omron HEM-9200T, along with the standard method for measuring BP, as outlined in the 2024 Thai Hypertension Society guidelines [46]. The researchers will require calibration of the automatic BP measurement using the clinical instrument testing center by the standard calibrator lab at the start of the intervention and during the study to ensure accuracy.

### Statistical Analysis

The analysis will include both the complete case and intention-to-treat analyses. The researcher will be using SPSS Statistics (IBM Corp) and Jamovi (GNU Affero General Public License and GNU General Public License) open-source statistical software to analyze quantitative data using the following statistical methods:

Descriptive statistics, including frequency, percentage, mean, and SD, were used to characterize the demographic data and sample characteristics.Repeated measures ANOVA will analyze changes in self-management behaviors across baseline, week 6, week 12, and week 24. Additionally, clinical outcomes measured at baseline, week 12, and week 24, including those that show significant differences at one or more time points, will be evaluated [47]. This method is based on data that meet assumptions, including normality of the dependent variable, no outliers, sphericity (equal variances across time points), and a balanced number of observations.In case data are missing or observations are unbalanced at each time point, linear mixed effects models will be used to evaluate changes in outcomes over time [48]. Researchers will set time as a fixed effect and individuals as random effects.Post hoc tests will be used to accurately determine the specific differences between time points, using a Bonferroni correction adjustment [47].

The hypothesis will be tested in a hierarchical approach. The primary outcome of self-management behaviors will be tested first at the α=.05 level. If significant, the first key secondary outcome, blood pressure, will be tested, and so on. For the set of secondary outcomes contributing to the main effect claim, the values will be adjusted using the Holm-Bonferroni method to control the family-wise error rate at α=.05.

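### The primary outcome is defined and powered as one baseline-to-week-12 change, but the planned analysis tests a four-visit time effect with Bonferroni post hoc tests and never says which test is the primary gate

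*Protocol article*

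**What the plan says.** Protocol article, Sample Size Calculation: "The primary outcome of this study is the change in the self-management behavior score from baseline to 12 weeks postintervention". The size rests on one comparison: "The sample size was calculated for a paired-samples within-group design using G*Power". For the effect, "a moderate effect size (Cohen *d*=0.5) was assumed"; at alpha 0.05 and 80% power "the required sample size to detect a change is 34", raised to 45 for 30% attrition.

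Protocol article, Statistical Analysis, on the same outcome: "Repeated measures ANOVA will analyze changes in self-management behaviors across baseline, week 6, week 12, and week 24". If data are missing or unbalanced, a linear mixed model with time as fixed effect replaces the ANOVA. On individual visits: "Post hoc tests will be used to accurately determine the specific differences between time points, using a Bonferroni correction adjustment". On the order of testing: "The primary outcome of self-management behaviors will be tested first at the α=.05 level". Blood pressure follows if that test is significant, then the remaining secondary outcomes. Neither the visit nor the contrast behind the 0.05 test is named.

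Two other places bear on the choice of visit. The Conclusions list self-management behaviors among primary outcomes assessed at the end of week 6. Study Components says the digital devices are used for the first 6 weeks, after which participants continue without them for another 6.

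**The concern.** A four-visit time effect asks whether any visit differs from any other. The stated primary question is whether week 12 differs from baseline. The one route to that contrast that the analysis section spells out is a multiplicity-adjusted post hoc test, which the sample size did not allow for.

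The device schedule makes this more than a formality. The Background asks whether short device use has an effect that carries on afterwards, so an improvement at week 6 that has faded by week 12 is the result the trial most needs to tell apart from success. An overall time test cannot do that. At stake are the meaning of a positive primary result and whether the secondary hierarchy opens.

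**Working it through.** **Inputs.** From Sample Size Calculation: d=0.5 on the paired difference, alpha 0.05, 80% power, 34 evaluable, 45 enrolled, 30% attrition. From Statistical Analysis: four visits and a Bonferroni correction. Week 12 is counted from the start of the intervention, as in Data Collection Procedures. Completers at the planned attrition: 45 × 0.70 = 31.5, so 31 or 32.

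**Step 1: reproduce the plan's figure.** Paired t test, two-sided: power = P(|T| > t(1−α/2, n−1)), with T noncentral t on n−1 df and noncentrality d√n. At n=34, d√n = 0.5 × √34 = 2.915 and the critical value is 2.035, giving power 0.808. The smallest n reaching 0.80 is 34, as stated. The protocol does not state sidedness; a one-sided test would need 27. What was powered is therefore a single, unadjusted, two-sided paired test.

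**Step 2: suppose the gate is the overall time effect.** Assume equal correlation between visits, scaled so that a paired difference has SD 1 (error variance 0.5). Let week 6 shift by 0.5 with weeks 12 and 24 at baseline.
- Sum of squared deviations of the four means: 0.25 × 3/4 = 0.1875.
- F noncentrality: n × 0.1875 / 0.5 = 0.375n, on 3 and 3(n−1) df.
- n=31: noncentrality 11.625, power 0.81. n=32: 12.0, power 0.82. n=34: 12.75, power 0.85.

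Simulation with 20,000 runs per scenario agrees (0.807, 0.822, 0.847). In the same runs at n=32 and 34, the week-12 pair at 0.05/6 was significant in about 1%, as it should be with no week-12 change.

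**Step 3: suppose the gate is the Bonferroni-adjusted week-12 pair.** Four visits give 4 × 3 / 2 = 6 pairs, so alpha = 0.05/6 = 0.0083. Baseline-referenced pairs only give 3, so alpha = 0.05/3 = 0.0167. The protocol gives no count. Power at d=0.5, by the formula in step 1:

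| Completers | Unadjusted 0.05 | 3 pairs | 6 pairs | 6 pairs, pooled ANOVA error |
|---|---|---|---|---|
| 31 | 0.77 | 0.60 | 0.49 | 0.54 |
| 32 | 0.78 | 0.62 | 0.51 | 0.56 |
| 34 | 0.81 | 0.65 | 0.55 | 0.59 |
| 45 (no attrition) | 0.91 | 0.80 | 0.72 | 0.75 |

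The pooled column uses 3(n−1) df. Requiring the overall test to pass first hardly changes the six-pair figures: about 0.51 at n=32 and 0.54-0.55 at n=34. Keeping 80% power with six pairs would take 52 evaluable, or 52/0.70 = 74.3, so 75 enrolled.

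**The case against.** **The gate may already be the right contrast.** Put the definition from Sample Size Calculation into the sentence on hierarchical testing, and the 0.05 test becomes the week-12 change, unadjusted. The ANOVA and post hoc tests would then only describe the time course. This is a fair reading and it removes both problems. But the analysis section does not say so: it assigns the outcome to a four-visit analysis and visit differences to Bonferroni. The Conclusions' week-6 placement means a reader cannot simply assume week 12.

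**The two consequences cannot both apply.** This stands in full. The false opening of the hierarchy needs the overall test as gate; the loss of power needs the adjusted pair as gate. A reader might infer that the trial suffers both, or that it has about 50% power for its primary question. The text supports neither. The 50% figure is the low end of a range, and needs six pairs and 31-32 completers.

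**The number of visits is unsettled.** Data Collection Procedures lists self-management at baseline, weeks 1 to 6 and week 12, without week 24. An analysis at baseline, week 6 and week 12 has three pairs, which is the milder column above.

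**The figures for 31-32 completers are complete-case.** The mixed model uses partial data and may recover a little power. It keeps the same unspecified time effect. Part of the loss at 31-32 completers comes from the attrition allowance and not from Bonferroni: the unadjusted test itself has 77-78% there.

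**The study is preliminary and an SAP may exist.** Hypothesis 3 covers weeks 6, 12 and 24, so an across-time model has a purpose, and the Discussion disclaims causal inference. That limits the harm. But the article commits to a primary method, a correction and a gating rule that do not, as written, test its stated primary outcome. That goes beyond omitted detail.

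**Conclusion.** The mismatch between the two sections is in the text and holds without any assumption. Its consequence is conditional.

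- **Overall time effect as gate:** a week-6-only shift of d=0.5 passes in about 81-85% of trials at 31-34 completers and opens blood pressure testing with no week-12 change. This assumes equal correlation between visits; it does not depend on the number of pairs.
- **Bonferroni-adjusted week-12 pair as gate:** power at d=0.5 and 31-34 completers is 49-55% with six pairs (54-59% with pooled ANOVA error) or 60-65% with three. It is 72-80% if all 45 are retained, so the stated 80% is reached only with full retention and three pairs.
- **Unadjusted week-12 contrast as gate:** 77-81% at 31-34 completers, close to the plan.

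Only the third matches the sample size, and the protocol does not state it. This should be settled before the data are analysed.

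**What to change.** In Statistical Analysis, name one primary test: week 12 minus baseline in the self-management score, by paired t test or as a contrast from the mixed model, two-sided alpha 0.05, no Bonferroni, with its 95% CI. State that this test is the gate for the hierarchy. Report the overall time effect and the week-6 and week-24 contrasts as secondary. Apply the multiplicity correction to those only and state the number of comparisons. Reconcile the Conclusions, which put self-management among the week-6 primary outcomes, with Sample Size Calculation.

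The cost is wording only, with no added participants or visits. The downside is that the test of any change over time loses primary status. If the sponsor prefers to keep the six-pair adjusted contrast as primary, the price is 52 evaluable and 75 enrolled instead of 34 and 45.

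### Sphericity is misdefined and a violation has no stated consequence, so error rates for change over time can be off, depending on a covariance the protocol does not give

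*Protocol article*

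**What the plan says.** All of this is in the Statistical Analysis section of the protocol article unless noted.

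- Main method for the primary outcome: "Repeated measures ANOVA will analyze changes in self-management behaviors across baseline, week 6, week 12, and week 24". The same method covers "clinical outcomes measured at baseline, week 12, and week 24".
- Among the assumptions on which the method is said to rest is "sphericity (equal variances across time points".
- Fallback: "In case data are missing or observations are unbalanced at each time point, linear mixed effects models will be used". Its structure: "Researchers will set time as a fixed effect and individuals as random effects".
- Post hoc comparisons are made "using a Bonferroni correction adjustment". The error term (pooled or specific to each pair) is not stated.
- Testing order: "The primary outcome of self-management behaviors will be tested first at the α=.05 level".

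The Sample Size Calculation section makes baseline to week 12 the primary change, requires 34 evaluable participants, allows for 30% attrition and enrols 45.

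**The concern.** The bracketed definition is wrong. Sphericity concerns the variances of differences between pairs of visits, not the variances at the visits. Visits here fall at 0, 6, 12 and 24 weeks. If correlation fades with time, or if baseline correlates less with follow-up than the follow-ups do with each other, the variances of the differences are unequal even when every visit has the same variance. An analyst applying the written definition would pass such data.

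The next step does not repair this. The switch to a mixed model depends on missing or unbalanced data, so non-sphericity alone leads nowhere. When the switch does happen, a model with a fixed time effect and only a random intercept gives every pair of visits the same correlation and, with complete data, the same standard error. The fallback would then carry at least as strong an assumption as the method it replaces.

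At stake are the p-values and interval widths for change from baseline, both for the primary outcome at the head of the testing order and for the week-24 comparisons. The Discussion also says that preliminary effect sizes will inform the later randomized trial.

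**Working it through.** **1. The plan's own figure.** A two-sided paired t-test with α=0.05 and d=0.5 (noncentral t) gives n=34, power 0.808, as stated. A single paired difference needs no sphericity assumption, so the sample size is not affected by this point.

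**2. Is the definition right?** Box's epsilon equals 1 under sphericity. With S the covariance matrix, C the centring matrix and A = CSC, ε = tr(A)² / [(k−1) tr(A²)], with k=4 visits.

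- All variances 1, correlation 0.8 per 6 weeks, decaying: ε=0.737. Equal variances are not sufficient.
- Variances 1.6, 2.0, 2.4, 2.8 with covariance a_i + a_j (a = 0.3, 0.5, 0.7, 0.9): ε=1.0. Equal variances are not necessary.

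**3. What can it do to error rates?** The article gives no SDs or correlations, so these patterns are assumptions, all with variance 1 at every visit:

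- (a) correlation 0.7 per 6 weeks, decaying (ε=0.79);
- (b) baseline with follow-up 0.4, follow-ups with each other 0.75 (ε=0.75);
- (c) compound symmetry (ε=1).

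A pooled-error contrast uses the average variance of a difference, 2(1 − mean ρ). The true variance for baseline versus visit j is 2(1 − ρ_0j). With ratio r = true/pooled, the large-sample error is P(|Z| > 1.96/√r).

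- (a) mean ρ = (0.7+0.49+0.2401+0.7+0.343+0.49)/6 = 0.4939; pooled 1.012. True: week 6 0.600, week 12 1.020, week 24 1.520. r = 0.593, 1.008, 1.501. Errors 1.1%, 5.1%, 11.0%.
- (b) mean ρ = (3×0.4+3×0.75)/6 = 0.575; pooled 0.85. True 1.2 at each visit. r = 1.412. Error 9.9% for each.

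Simulation under no change (20,000 datasets, n=34, complete data, where the random-intercept contrast equals the pooled-error contrast; Monte Carlo SE about 0.15 points at 5%):

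| | Omnibus | Week 6 | Week 12 | Week 24 |
|---|---|---|---|---|
| (a) | 6.4% | 1.3% | 5.4% | 10.9% |
| (b) | 6.3% | 10.0% | 9.6% | 9.8% |
| (c) | about 5% | about 5% | about 5% | about 5% |

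The contrasts are unadjusted 5% tests. Paired t-tests on the same data stay at about 5% throughout. In milder forms of (b), with baseline correlation 0.5 or 0.6, week 12 is 8.6% or 7.8%.

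**4. With the planned Bonferroni adjustment.** Four visits give six pairs; 0.05/6 = 0.83% each. With a pooled error term, week 12 rejects 0.9% in (a) and 2.7% in (b), and week 24 in (a) rejects 3.3%.

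**5. The fallback with dropout.** Random-intercept REML model, 45 enrolled, 30% dropout completely at random, 1,500 runs (SE about 0.6 points at 5%), unadjusted:

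| Assumed truth | Omnibus | Week 12 | Week 24 |
|---|---|---|---|
| Compound symmetry, ρ 0.5 | 5.4% | 5.4% | 5.3% |
| Decay 0.6 per 6 weeks | 6.1% | 6.7% | 9.6% |
| Decay 0.8 per 6 weeks | 7.5% | 4.9% | 13.1% |
| Random slope | 6.6% | 5.5% | 13.2% |

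**6. Clinical outcomes (weeks 0, 12, 24).** At n=34, decay 0.8 and random slope give an omnibus error of 5.7% and 5.9%, with unadjusted pooled contrasts of 3.4% and 3.0% at week 12 and 9.1% and 10.2% at week 24.

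**The case against.** The strongest reply is that everything beyond the definition is conditional. No covariance is given, and under compound symmetry nothing goes wrong. That stands: this is a risk, not a demonstrated error rate.

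Four stronger readings are tempting, and the article does not support them.

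- *The primary test has a 10% false-positive rate.* That arises only under pattern (b), with a pooled error term and no adjustment. Under (a) week 12 is 5.4%, and with unequal variances growing over time it is conservative (2.2% to 3.8%). The plan also adjusts post hoc tests, and pair-specific tests would hold their level.
- *The testing order opens on an inflated contrast.* The text says the primary outcome is tested first at 0.05, but not whether by the omnibus test or a contrast. If by the omnibus test, the error is about 6.3% in both main scenarios.
- *The mixed model has only a random intercept.* This is the natural reading of "Researchers will set time as a fixed effect and individuals as random effects", but the wording does not exclude a random slope or a residual covariance structure.
- *The lack of a named correction or covariance structure is itself a fault.* Such detail is commonly left to an analysis plan, which is not shown. The same applies to which analysis is primary in "The analysis will include both the complete case and intention-to-treat analyses", which is in any case a separate question.

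The Discussion also presents the study as preliminary and warns against causal claims, which limits the harm from modest inflation. None of this rescues the definition or the trigger: both are stated rules, not omissions.

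**Conclusion.** The point holds in a limited form. The definition of sphericity is wrong as written, and applying it literally can pass non-spherical data and reject spherical data. A violation has no stated consequence, because the mixed model is triggered only by missing or unbalanced data. Since 30% attrition is allowed for, that model is the likely operative analysis, and read as a random-intercept model it needs compound symmetry.

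Error rates *can* therefore be wrong; the documents do not show that they *are*. Across the non-spherical patterns tried, omnibus inflation is modest (about 5.5% to 7.5%). The larger distortion is in individual contrasts: too few rejections at week 6 under fading correlation, too many at week 24, and too many at week 12 only if baseline is the less correlated visit. These sizes rest on assumed covariances, a pooled or random-intercept error term, and n=34 complete or 45 with random dropout. The point should be corrected before analysis, but it does not threaten the design or the sample size.

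**What to change.** Correct the definition to equal variances of all pairwise differences between visits. Make one model the primary analysis whether or not data are missing: a linear mixed model with time categorical (0, 6, 12, 24 weeks), an unstructured covariance across visits (4×5/2 = 10 parameters), REML, and Kenward-Roger or Satterthwaite degrees of freedom. Name in advance a structured covariance to fall back on if it does not converge. Use the same model with three visits for the clinical outcomes.

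If repeated measures ANOVA is kept anywhere, apply the Greenhouse-Geisser correction (omnibus error 4.4% to 5.0% in every scenario tried) and use pair-specific error terms for post hoc contrasts (4.7% to 5.4% before adjustment).

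The cost is a change of wording, a few degrees of freedom and slightly more programming. Recruitment, visits and sample size are unaffected.
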